### Interventional method

2.3

The fiber dietary supplement will be administered randomly to half of the study patients, in open-label mode. The BD patients will receive either inulin supplementation or placebo. The participants were recommended to consume the powder during the breakfast by mixing it to 150 mL of warm water and then stirring up the powder until dissolved.

At the starting point and 3 months later, for each BD patients will be collected: samples for the assessment of oral/fecal microbiota, breath samples, BMI, disease duration, clinical phenotype and ocular, articular or mucocutaneous involvement and information about eating habits. Patients in the treatment arm will assume 5 g per day of inulin in addition to their ordinary diet and in a randomized order. The 5 g dose was chosen after considering the amounts of prebiotics that would be sufficient to induce positive and significant changes in the gut microbiota, but low enough to avoid adverse effects and minimize gastrointestinal discomfort (Bouhnik et al., 1999; Kolida et al., 2007).

All data obtained, will be analyzed with innovative AI methods, in order to evaluate the conditions of eubiosis/dysbiosis and to identify potential microbial and metabolic markers linked to BD, to eating habits of patients and to a soluble fiber dietary supplement administration.

### Outcome measure

2.5

In the initial phase of our study, our primary focus lies in a data-driven analysis designed to distinguish, at the 3-month period, two distinct patient groups based on microbiota and volatilome profiles. The first group undergoes traditional treatment with soluble fiber intake (inulin), while the other receives only traditional treatment. This outcome is propelled by the application of Explainable Artificial Intelligence (XAI) techniques, aiming to uncover the pivotal features contributing to the differentiation between the two groups. Our investigation extends to understanding the global and local importance of these features, providing insights into the personalized metabolic responses to treatment.

The outcome measures considered are summarized in Table 1. Integrating these biological and clinical parameters using a data-driven approach, our objective is to paint a comprehensive picture of the personalized metabolic markers associated with Behçet’s disease. This dual-phase evaluation not only enriches our understanding of microbiome and metabolome nexus with the disease but also lays the groundwork for targeted interventions and more detailed treatment strategies.

**Table 1 tab1:** Biological and clinical outcome measures considered in the presented protocol study.

Biological outcome measures	Erythrocyte sedimentation rate (ESR)
	C-reactive protein (CRP)
Clinical outcome measures	Behçet’s Disease Current Activity Form (BDCAF) – measure of disease activity
	Krause Total Severity Score – measure of disease severity
	Short-form (SF)-36 quality of life (QoL) scale – measure of disease QoL

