
Keeping all these evidence in mind, the proposed study is aimed to: (i) establish correlations between oral and intestinal microbiota, fecal and salivary volatilome, breath and phenotypic features of human hosts, affected by BD, active and/or in remission; (ii) identify, through cluster analysis methods of metabolites, different groups of patients affected by BD; (iii) identify some taxonomic units of oral and fecal microbiota and metabolic markers that majorly contribute to the prediction of different clinical outcomes (e.g., number of active mucosal lesions, remission following the Behçet Disease Current Activity Form (BDCAF)); (iv) identify, with XAI methods (Bellantuono et al., 2022), some personalized metabolic markers that, for each patient, contribute to the prediction of his/her clinical outcome (personalized medicine); (v) evaluate the effects of soluble fiber intake (inulin) on eubiosis/dysbiosis conditions of oral and intestinal microbiota and on endogenous production of butyrate; and (vi) establish correlations between eating habits and clinical outcome of patients.

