### Data analysis

2.8

Data collected by investigators will include volatilome, oral/fecal microbiota, body mass index (BMI), disease duration, clinical phenotype and ocular, articular or mucocutaneous involvement.

The microbiota can be characterized in three different ways: alpha diversity metrics, relative abundance of phylotypes for each specimen and community state types (CST). Alpha diversity metrics, which represent the variety and richness of organisms in a specimen, and relative abundance of microbes will be analyzed through supervised machine learning algorithms as Random Forest or XGBoost classifiers. Supervised machine learning is a category of machine learning where the algorithm is trained on a labeled dataset, which means that each example in the training data is associated with the correct output or target. The algorithm learns to make predictions or decisions based on input data by generalizing from the labeled examples it has seen during training. Moreover, the XAI algorithm “SHapley Additive exPlanations” (SHAP) will be used to detect for each patient, which features are more important for the ML algorithm in its classification (Bellantuono et al., 2023; Novielli et al., 2023). SHAP is an algorithm used in machine learning to explain the predictions made by complex models, particularly for models like XGBoost, Random Forest, neural networks, and others. It provides interpretable explanations for individual predictions, helping users understand why a particular prediction was made. The third characterization, i.e., CST, which groups samples according to the composition of the microbiota, will be analyzed through the application of complex networks (CN). This mathematical method, also known as complex systems or complex networks theory, is a branch of network science that studies systems characterized by a large number of interconnected components or nodes, and the patterns and properties that emerge from these connections. In our case, interactions between microbiome and its host are complex phenomena, and to better understand this kind of complex interactions and to map microbiome behavior is of fundamental importance to have the possibility to model these interactions through CN. Modules of this complex biological network are key organizational elements for the network itself. To detect modular organizational structures of a complex network, community detection unsupervised algorithms will be used.

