### Anticipated results

3.2

This will be the first study that tries to understand the complex relationships between diet, intestinal microbiota and human breath in patients affected by BD through an innovative approach based on AI methods (Golob et al., 2023; Novielli et al., 2023; Papoutsoglou et al., 2023). Such an understanding can represent a significant step forward toward the comprehension of pathogenetic mechanism at the basis of BD onset and the identification of microbial, metabolic and immunological factors and therapeutic biomarkers able to control treatment outcome and to better understand how the such a treatment can modify microbiome. In fact, intestinal dysbiosis has been linked to inflammatory diseases (Douzandeh-Mobarrez and Kariminik, 2019) and recent studies have demonstrated that therapeutic treatment in rare rheumatological diseases can modify subclinical intestinal inflammation and dysbiosis (Manasson et al., 2020), highlighting the bidirectional nature of this correspondence. Furthermore, this study will evaluate for the first time with multivariate models if microbiome and breath modulation through the diet can improve disease activity in patients with BD under treatment. This analysis could enable us to find valuable markers to identify responders and non responders, allowing treatment optimization and a personalized therapeutic approach. This study could be also useful to analyze diet effects on BD activation and/or remission. Going into details, network approach thought for this study is aimed to catch functional structure of dynamic processes happening between microbiome and human host, to identify the coexistence of different microorganisms, to trace relationships between microorganisms and to identify cohesive groups that play fundamental roles in maintaining functional relationships in the global network during the treatment. Identification and quantification of some of the topological properties of the network modules can provide important information on microbiome interactions and on their relationship with possible disorders and anomalies in inflammatory and pathological states. Specifically, co-occurrence patterns and identified polymicrobial interactions will be related with other clinical and phenotypical data to detect correlations between network functional and structural properties and biological and pathological profiles in different starting conditions. This integrative approach is completely innovative, since it will allow to highlight some connectivity patterns linked to inflammatory states, pathologies, etiological agents and even the organisms responsible for pathology transmission.

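### The effect of inulin on individual taxa and volatile compounds is to be read from feature importance in an arm classifier, which is not the size of a change and gives no estimate or interval

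*Protocol article*

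**What the plan says.** Aim (v) in the Introduction is to "evaluate the effects of soluble fiber intake (inulin) on eubiosis/dysbiosis conditions of oral and intestinal microbiota" and on endogenous butyrate production. Section 2.5 (Outcome measure) states the primary analysis: "our primary focus lies in a data-driven analysis designed to distinguish, at the 3-month period, two distinct patient groups based on microbiota and volatilome profiles". Explainable AI is applied to it, "aiming to uncover the pivotal features contributing to the differentiation between the two groups". The same section extends this to "understanding the global and local importance of these features, providing insights into the personalized metabolic responses to treatment". Section 2.3 gives the AI step the task to "identify potential microbial and metabolic markers linked to BD, to eating habits of patients and to a soluble fiber dietary supplement administration", and section 2.1 says much the same.

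Section 2.8 (Data analysis) names the tools. Alpha diversity and "relative abundance of microbes will be analyzed through supervised machine learning algorithms as Random Forest or XGBoost classifiers". SHAP then shows, for each patient, "which features are more important for the ML algorithm in its classification". Community state types go to an unsupervised network analysis. Section 2.9 adds PCA and Boruta, both for feature reduction.

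Sections 2.5 and 2.8 describe no between-arm difference for any single taxon or compound. Section 2.4 sizes the trial on a difference between two groups in beta-diversity and mean OTU presence, but section 2.8 does not take that comparison up.

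**The concern.** Aim (v) is a question about effect: what does inulin change, and by how much? Importance in a classifier answers a different question: what does this model use to tell the arms apart? Section 2.8 itself describes SHAP as importance to the algorithm, while section 2.5 presents the same quantity as metabolic response to treatment.

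The two can differ when features move together. If inulin raises a group of related taxa, a boosted model may take most of its information from one or two of them and give the rest little credit, although all have changed. Section 3.2 expects such structure, since the network analysis there is meant "to identify the coexistence of different microorganisms, to trace relationships between microorganisms and to identify cohesive groups". The rationale in the Introduction and section 3.1 rests on a functional group of this kind, the butyrate producers.

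The randomised contrast is where this trial can say what inulin does. Reported only as importance, it would yield a ranked list without direction-and-size estimates or intervals, and the ranks of related taxa could be partly arbitrary.

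**Working it through.** **Size of the comparison.** Section 2.4 gives effect size 0.80, alpha 0.05, power 0.80 and 26 patients. Read as 26 per group, this reproduces: the two-sided two-sample t-test needs 25.5, so 26. Allowing for 20% dropout, 26 / 0.80 = 32.5, so 33 per group against the stated 35. From 70 enrolled, 70 × 0.80 = 56 complete, or 28 per arm.

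**Assumptions.** The article gives no number of features, number of changed features or correlation. The main simulation assumed 200 features, normal on a transformed scale, 10 of them shifted by 0.80 SD, and 28 per arm. Correlation among the ten was 0, 0.3 or 0.6, with 150 runs per setting. XGBoost used default settings and one fit per dataset.

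**How many of the 10 changed features reach the top 10:**

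| Ranking by | corr. 0 | corr. 0.3 | corr. 0.6 |
|---|---|---|---|
| XGBoost, SHAP | 5.1 | 3.5 | 2.6 |
| Random Forest | 6.0 | 5.8 | 5.6 |
| Difference in means | 7.0 | 7.1 | 7.2 |

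The loss with correlation is clear for XGBoost, slight for Random Forest and absent for the difference in means. With 100 features and correlation 0.3, XGBoost gives 4.0 against 7.7 for the difference in means.

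**Different assumptions.** A second simulation used 100 features, 5 changed by 0.80 SD, and 28 or 35 per arm, with 45 runs per setting. The share of changed features outside the XGBoost top 10 was 25 to 35% when independent and 63 to 72% at correlation 0.9. For Random Forest it was 14 to 33%, with little dependence on correlation. The direction is the same; the sizes follow the assumptions.

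**Exact zeros.** In the main setting, a single XGBoost fit gave SHAP exactly zero to 2.5, 4.0 and 5.1 of the 10 changed features at correlation 0, 0.3 and 0.6. A 40-run repeat gave 2.3, 4.1 and 5.0. When SHAP was pooled over held-out folds of 10 × 5-fold cross-validation, these fell to 0.0, 0.1 and 0.1, but the low ranks remained (top 10 holding 5.9, 4.5 and 2.8). Random Forest gave no exact zeros.

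**Boruta.** A simplified version confirmed 3.8 and 2.9 of 10 at correlation 0.3 and 0.6 (16 runs per setting). In the second simulation a Boruta-style filter confirmed 16 to 32% of the changed features at 0.80 SD. It does not make up the loss at this size.

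**What a per-feature estimate gives.** In SD units the standard error of a between-arm difference is √(2/28) = 0.267, so the 95% half-width is about 2.005 × 0.267 = 0.54. If the baseline value correlates at 0.5 (assumed), the standard error is √(2/28 × (1 − 0.25)) = 0.231 and the half-width about 0.46. These do not depend on how the taxa correlate with each other.

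**What false discovery control then declares.** With Benjamini-Hochberg at 10% over 200 features, separate simulations found about 4.2 to 5.0 of the 10 changed features without baseline and about 5.8 to 6.9 with it. Over 100 features with 5 changed, at 5% and without baseline, the share declared at 28 per arm was 0.26 to 0.35.

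**The case against.** **The article promises no complete list.** It aims to find pivotal features and potential markers, and aim (v) speaks of eubiosis and dysbiosis, not of each taxon. A reader might infer that taxa with low or zero importance will be reported as unaffected by inulin. The document states no such rule, so that inference is not supported. What remains is that section 2.5 does treat importance as information about treatment response.

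**A per-feature table is a detail that an article may leave to the analysis plan.** This is true of the prevalence filter, the scale and the error control, and a separate plan may contain them. The point does not rest on their absence, however. It rests on the reading of importance that section 2.5 states.

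**Co-varying groups have their own analysis.** Section 2.8 plans networks with community detection, and section 3.2 relates the patterns to clinical data. This is a fair reminder that importance is not the only view of such groups, but the network step as described estimates no between-arm change.

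**Zero importance is mostly an artefact of a single boosted fit.** This stands. Section 2.9 plans repeated cross-validation, and pooling SHAP over folds almost removes the zeros. The pooling is itself an assumption, because section 2.9 speaks only of averaging performance metrics. It is also not supported to say that the plan would miss most of any co-varying group: section 2.8 allows Random Forest, where correlation hardly matters.

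**The benchmark favours the remedy.** The simulated data are normal with pure mean shifts; sparse, compositional abundances were not tested. After false discovery control the remedy also leaves many changed features undeclared. Both stand, and they are the reason to report intervals as well as a declared list.

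**Conclusion.** The point holds as one of interpretation and reporting. Importance in the arm classifier is not an effect size and has no interval, whichever classifier is used; this part needs no simulation. The risk of low rank for changed, co-varying features applies chiefly to XGBoost: about 3.5 and 2.6 of 10 in the top 10 at correlation 0.3 and 0.6, against about 7 for a difference in means. These figures assume 28 per arm, a 0.80 SD shift, 200 features with 10 changed, normal data and one default fit. For Random Forest the correlation effect is small. The documents do not support a claim that affected taxa will be declared unaffected, or that zero importance would be common after cross-validation. This is a worthwhile, cheap improvement, and it does not make the classifier analysis invalid for its own purpose.

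**What to change.** In sections 2.5 and 2.8, state that the effect of inulin on individual taxa and volatile compounds is reported as follows. For each feature passing a prevalence filter, give the between-arm difference at 3 months on a log or log-ratio scale, adjusted for the feature's baseline value, with a 95% interval. Control the false discovery rate within each specimen type, for example by Benjamini-Hochberg at 10%. Report all the estimates with their intervals, and not only the features declared.

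Keep the classifier and SHAP as a description of how the model separates the arms. Add that importance is not effect size and that low importance is not evidence of no effect.

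The cost is some wording and one more table per specimen type, from samples already planned at baseline and 3 months. The downside is that, with about 28 completers per arm, false discovery control will leave many truly changed features undeclared: roughly half in the main simulation, and more under the stricter 5% level without baseline.

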### Adverse events

2.6

Symptoms relating to gastrointestinal discomfort (abdominal discomfort, diarrhea, constipation, bloating, and flatulence) are widely reported in human prebiotic feeding studies, but they remain very mild at recommended intakes (Rumessen et al., 1990; Gibson et al., 1995). Based on the literature, 16 g of inulin-type fructans per day induces no or only minor gastrointestinal symptoms in healthy or diseased adults (Cani et al., 2009; Birkeland et al., 2020). Taking potential side effects into consideration, 5 g dose was preferred over higher doses due to a precautionary principle.

### Data recording and data monitoring

2.7

Follow-up assessments and data collection will be undertaken at the U.O.C. Reumatologia Universitaria of the Policlinico Hospital, Bari, Italy, by trial personnel.

### Data analysis

2.8

Data collected by investigators will include volatilome, oral/fecal microbiota, body mass index (BMI), disease duration, clinical phenotype and ocular, articular or mucocutaneous involvement.

The microbiota can be characterized in three different ways: alpha diversity metrics, relative abundance of phylotypes for each specimen and community state types (CST). Alpha diversity metrics, which represent the variety and richness of organisms in a specimen, and relative abundance of microbes will be analyzed through supervised machine learning algorithms as Random Forest or XGBoost classifiers. Supervised machine learning is a category of machine learning where the algorithm is trained on a labeled dataset, which means that each example in the training data is associated with the correct output or target. The algorithm learns to make predictions or decisions based on input data by generalizing from the labeled examples it has seen during training. Moreover, the XAI algorithm “SHapley Additive exPlanations” (SHAP) will be used to detect for each patient, which features are more important for the ML algorithm in its classification (Bellantuono et al., 2023; Novielli et al., 2023). SHAP is an algorithm used in machine learning to explain the predictions made by complex models, particularly for models like XGBoost, Random Forest, neural networks, and others. It provides interpretable explanations for individual predictions, helping users understand why a particular prediction was made. The third characterization, i.e., CST, which groups samples according to the composition of the microbiota, will be analyzed through the application of complex networks (CN). This mathematical method, also known as complex systems or complex networks theory, is a branch of network science that studies systems characterized by a large number of interconnected components or nodes, and the patterns and properties that emerge from these connections. In our case, interactions between microbiome and its host are complex phenomena, and to better understand this kind of complex interactions and to map microbiome behavior is of fundamental importance to have the possibility to model these interactions through CN. Modules of this complex biological network are key organizational elements for the network itself. To detect modular organizational structures of a complex network, community detection unsupervised algorithms will be used.

### Comprehensive methodology for data challenges

2.9

To ensure a robust evaluation of our models, we will implement a cross-validation strategy. Cross-validation involves partitioning the dataset into subsets, training the model on some of these subsets, and testing it on the remaining subset. This process will be repeated multiple times, and the performance metrics will be averaged. This approach ensures that our models generalize well and helps prevent overfitting.

To handle the possible presence of missing values, we will adopt a two-fold approach:

*Variable Selection*: Variables with a relatively low percentage of missing values (below a defined threshold, e.g., 30%) will be considered to maintain data quality.*Imputation Techniques*: For variables exceeding the threshold, established imputation techniques will be employed. Additionally, we will use imputation methods such as replacing missing values with the mean or maximum of the respective variable. Importantly, these techniques will be applied separately to the training and testing datasets to prevent data leakage and ensure model generalization to unseen data.

We would also like to highlight the utility of the XGBoost algorithm, which inherently handles missing values in tree algorithms by learning branch directions during training.

To handle the potential limitation in the number of available patterns compared to the number of features considered, which could lead to overfitting, we will address the issue through the implementation of two robust techniques: data augmentation and feature reduction.

*Data Augmentation*: The data augmentation strategy aims to artificially amplify the quantity of training samples for deep learning models, emulating the distribution of the original dataset. This becomes especially advantageous when confronted with the constraint of a limited size in the training dataset. By introducing more diverse instances, it facilitates the model in generalizing more effectively, tackling the challenge posed by smaller training datasets. Essentially, it functions as a preprocessing technique and a type of regularization, significantly enhancing model performance and mitigating the risk of overfitting. Furthermore, the integration of Generative Adversarial Networks (GANs) into data augmentation further expands its capabilities. GANs can be employed to simulate data, generating synthetic instances that closely resemble real data. This innovative use of GANs not only augments the dataset but also introduces a layer of complexity and realism, ultimately contributing to the model’s ability to generalize and perform effectively across diverse scenarios (Creswell et al., 2018).*Feature Reduction*: Feature reduction is a crucial aspect of our approach. Techniques such as Principal Component Analysis (PCA) (Song et al., 2010) and wrapper methods like Boruta (Kursa et al., 2010; Bellantuono et al., 2023) will be employed. These methods effectively reduce the dimensionality of the feature space, allowing us to train models even with a limited number of instances. This not only aids in computational efficiency but also contributes to model interpretability.

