
Data from human microbiome and breath are inherently complex, noisy and highly variable because several factors such as diet, sex, hormonal status, drugs, habits, etc. could affect them. So, non-standard analytical methodologies are needed to extract their clinical and scientific potential. Nowadays, a lot of Artificial Intelligence (AI) methods, such as Machine Learning (ML) or complex networks, are available to catch this complexity. In particular, AI methods use several layers of linear and/or non-linear calculating units to understand the data they manipulate and to learn “patterns” from the same data. This learning can be used to classify the observations or to make predictions on them (Hassabis et al., 2017; Amodeo et al., 2021). The specific AI model to be used is chosen according to its capability to maximize prediction accuracy but requires, on the other hand, an increased complexity of the model itself, that makes it less interpretable (Shaban-Nejad et al., 2021) (e.g., “black boxes”). To overcome these drawbacks, coming from more complex models, and to adapt ML utilization to clinical contexts, eXplainable Artificial Intelligence (XAI) techniques have been introduced, that provide explanations for decisions the algorithm takes and for the risk scores calculated for every subject studied. Such a gain in interpretability for the chosen model is converted in the possibility to understand the main reasons standing behind a prediction and to point out the factors that majorly affect clinical risk scores at individual level. This approach is perfectly placed in an innovative concept of Personalized Medicine that requires the help of AI techniques.

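### Section 2.9 relies on one cross-validation loop while leaving model choices open; if the averaged metric also picks the model, apparent arm separation is inflated by about 2 to 5 accuracy points for two to four candidates.

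*Protocol article*

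**What the plan says.** Section 2.5 (Outcome measure) sets the primary focus: a data-driven analysis to "distinguish, at the 3-month period, two distinct patient groups based on microbiota and volatilome profiles". One group takes inulin with standard treatment and the other takes standard treatment alone. SHAP is then to show which features drive the separation, overall and for each patient.

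Section 2.8 (Data analysis) says that alpha diversity and relative abundances "will be analyzed through supervised machine learning algorithms as Random Forest or XGBoost classifiers". Section 2.9 allows missing values to be filled with either the mean or the maximum of a variable, and adds that XGBoost can handle them without filling. For feature reduction it plans PCA together with "wrapper methods like Boruta". It also plans data augmentation, within which "GANs can be employed to simulate data, generating synthetic instances that closely resemble real data".

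Validation is described once, in section 2.9. The data are partitioned, the model is trained on some parts and tested on the remaining one, and "This process will be repeated multiple times, and the performance metrics will be averaged". The section says that this makes the models generalise and guards against overfitting. Its leakage safeguard is stated for imputation only.

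The Introduction, discussing AI methods in general, says: "The specific AI model to be used is chosen according to its capability to maximize prediction accuracy".

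**The concern.** Cross-validation gives a fair estimate for a procedure fixed in advance. Once several candidates are scored on the same folds and the best score is both the reason for the choice and the reported result, that result is the maximum of several noisy estimates, and its expectation exceeds the winner's true performance. Fitting every preprocessing step inside the training folds does not cure this. Repeating the partition and averaging reduces partition noise, but the same patients are still used both to choose and to report.

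Two conclusions are at stake. Classifier performance is the evidence offered that inulin changes the profiles, so optimism there reads as an effect of inulin. SHAP then explains the chosen model, so a model that won partly on noise yields markers that are partly noise.

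**Working it through.** **Inputs from the protocol (section 2.4)**
- 70 patients, 35 per arm, 20% dropout. Completers: 70 × 0.80 = 56, or 28 per arm.
- The stated 26 patients (alpha 0.05, power 0.80, effect size 0.80) reproduces as a per-group figure: a two-sided two-sample t-test with 26 per arm has power 0.807.
- The plan states no target accuracy, AUC or cut-off for separation, so there is no performance figure to reproduce.

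**Candidates**
- Random Forest or XGBoost: 2.
- Crossed with mean or maximum fill: 2 × 2 = 4.
- PCA, Boruta and augmentation are worded as planned steps and are not counted as alternatives.

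**Noise in one estimate.** With true accuracy 0.50, a binomial approximation gives SE = √(0.25/N).
- N = 70: √(0.25/70) = 0.060.
- N = 56: √(0.25/56) = 0.067.

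**Expected maximum.** For M equally correlated normal estimates, optimism ≈ SE × √(1 − ρ) × e(M). Here e(2) = 1/√π = 0.564 and e(4) = 1.029. The correlation ρ is an assumption. A null simulation of six Random Forest and XGBoost pipelines gave a mean ρ of 0.42; 0.7 and 0.9 represent more similar candidates. At N = 70:

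| ρ | best of 2 | best of 4 |
|---|---|---|
| 0.42 | 0.060 × 0.762 × 0.564 = 0.026 | 0.060 × 0.762 × 1.029 = 0.047 |
| 0.7 | 0.060 × 0.548 × 0.564 = 0.019 | 0.060 × 0.548 × 1.029 = 0.034 |
| 0.9 | 0.060 × 0.316 × 0.564 = 0.011 | 0.060 × 0.316 × 1.029 = 0.020 |

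**Simulation with no arm effect.** Stratified 5-fold cross-validation was used, with all feature reduction inside the training folds. The feature set (100 oral, 100 fecal, 60 volatile compounds) is an assumption.

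Mean accuracy, simple learners, 400 null data sets per N, candidates drawn at random from 24 pipelines:

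| | N = 70 | N = 56 |
|---|---|---|
| one fixed pipeline | 0.501 | 0.502 |
| best of 2 | 0.525 | 0.527 |
| best of 6 | 0.553 | 0.559 |
| best of 12 | 0.564 | 0.576 |
| best of 24 | 0.578 | 0.589 |
| nested selection among 24 | 0.501 | 0.506 |

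Random Forest and XGBoost, each with PCA or a univariate filter, N = 70, 155 null data sets: one fixed pipeline averages 0.503. The best of four on one 100-feature block averages 0.553.

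The formula at ρ = 0.42 (0.526 and 0.547) and the simulations (0.525 and 0.553) agree on about 2 to 5 points for two to four candidates. Nested selection brings the mean back to about 0.50.

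**The case against.** The strongest reply is that the document never says the averaged metric picks a winner. The Introduction sentence is background on the trade-off between accuracy and interpretability that motivates SHAP. Section 2.9 presents cross-validation as a way to evaluate models, in the plural; every model might be reported, or one fixed in advance. A fuller protocol or analysis plan might nest the loops, and an article may leave that detail to it.

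Much of this stands. Using one loop for both choice and reporting is an inference, and the point is therefore conditional. What remains is that section 2.9 attaches a general assurance to a single loop while real alternatives stay open, and the assurance fails if the loop also selects.

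A reader might infer something stronger: that the plan commits to taking the best of many pipelines and so has a known false-positive rate. With six pipelines at 28 per arm, a null simulation gave a mean best AUC of 0.60, and in 22% of runs at least one pipeline beat its own 95% null cut-off. The documents do not support reading this as the plan's error rate:
- Six or more pipelines is a reviewer's construction. PCA, Boruta and augmentation are planned together, and running without reduction is not proposed.
- Sections 2.5, 2.8 and 2.9 set no test, alpha or cut-off for declaring separation.

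The realistic size is also modest. The simulated alternatives stand in for those in the text. Pipelines that differ only in mean or maximum fill may be more highly correlated, and at ρ = 0.9 the optimism is only about 1 to 2 points.

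**Conclusion.** The point holds in conditional form. If the averaged metric from the single loop chooses among the open options and is then reported, the performance quoted for the primary arm separation is biased upward, and the statement that this loop secures generalisation is not justified.

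With no arm effect, the optimism is about 2 to 5 accuracy points for two to four candidates (0.525 to about 0.55, against 0.50). It is nearer 1 to 2 points if the candidates are very similar, and 8 to 9 points if 24 are tried. These sizes rest on the assumed number of pipelines, their correlation and the feature set. Given such selection among imperfectly correlated candidates, the direction does not. No error rate is claimed. The change is worth making because it is cheap and affects what can be concluded about inulin and the SHAP markers.

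**What to change.** In section 2.9, do one of the following:
- Name one complete pipeline (classifier, reduction method and settings, fill, augmentation) before the 3-month data are analysed.
- Make every data-driven choice in an inner loop within each outer training set, and report only outer-fold performance.

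In either case, judge separation against a null distribution from permuted arm labels, repeating the whole procedure, including any selection, in each permutation. Nesting alone is not enough: under the null with 24 candidates it still gave accuracy of 0.60 or more in 8% (N = 70) and 12.5% (N = 56) of data sets, so a raw accuracy of that size is weak evidence. Remove the statement that single-level cross-validation ensures generalisation.

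The cost is one paragraph, more computing time, and a lower, slightly more variable reported performance. No extra patients or samples are needed.
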